Currently, clinical decision-making is conducted by a multi-professional care team which can consist of a psychiatrist, residents, nurses, clinical psychologist, social worker, counsellor, and support worker (25). Although this collaboration is beneficial in many respects (26), is typically costly and results in long wait times (6). A previous framework using real patient data has demonstrated the cost-effectiveness of using machine learning in clinical decision-making (27). The use of machine learning in healthcare has significantly increased over the past few years. In the context of clinical decision-making, machine learning algorithms use large data sets from an array of sources to assist healthcare providers in making rapid and informed decisions (28). To further understand symptom severity and increase treatment efficacy, many researchers have tried to implement supervised machine-learning approaches to identify patient characteristics that may be associated with poor treatment outcomes and develop a treatment for patients (29–32). These novel decision-making algorithms aim to mimic human decision-making to help with objective and accurate evaluation of each patient’s needs (33). This technology can make personalized care a possibility, particularly in cases where clinical decision-making by a care team is not feasible or results in prolonged wait times. Overall, the novelty of machine learning in healthcare demands greater exploration and understanding of responsible use (34).

The goal of this study is to develop a machine learning algorithm that can identify the intensity of care an individual needs based on their probability of dropping out from treatment. This algorithm is expected to be comparable to the clinical decision-making process. It is expected to indicate the appropriate level of care for an individual experiencing depression to make treatment efficient and effective. We believe that the integration of AI-driven clinical decision-making would make mental health care delivery more scalable, accessible, and affordable while remaining highly personalized and effective. To make this possible, we need to (1) make objective and quantified evaluations of patients’ mental status and their needs, (2) utilize a decision-making algorithm that allocates the right level of care for each patient, and (3) demonstrate that this method of care delivery can enhance the quality of mental health care and reduce costs.

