## Objectives

2

The primary objective of this study is to evaluate the effectiveness of the suggested level of care made by the AI compared to the healthcare team and the effectiveness of the stratified care model. This will be assessed using the change in the severity of depressive symptoms using the Patient Health Questionnaire – 9 Item (PHQ-9) (35) and Quick Inventory of Depressive Symptoms (QIDS) (36) scores, and the quality of life and functioning using Assessment of Quality of Life (AQoL-8D) (37) scores between the start and the end of the 13-session e-CBT program.

The secondary objectives include evaluating compliance and treatment completion using the number of sessions completed by each participant and evaluating the time and cost commitment of initial assessments (i.e., manual participant stratification by the healthcare team vs. the AI) and the different care intensities (i.e., only e-CBT, e-CBT + phone calls, or e-CBT + video calls). We will also evaluate the functional consequence of our interventions on participant quality of life via Quality-adjusted life years (QALY)s (38). Throughout the study, QALY estimates will be derived from AQoL-8D scores using the area under the curve method (39, 40). Outlined below are the research questions and the corresponding study hypotheses:

1 Will participants with major depressive disorder (MDD) assigned to an e-CBT program by an AI show similar outcomes in depressive symptoms at 3 months to those allocated to an e-CBT program decided by a team of healthcare professionals?

– We hypothesize that the outcomes in depressive symptoms of treatment arm 1 will be comparable to the outcomes of treatment arms 2 and 3 following e-CBT treatment.

2 How does AI-based clinical decision-making compare to that of a multi-professional healthcare team when allocating individuals with depression to an e-CBT program with different degrees of care intensity?

– We hypothesize that AI-based clinical decision-making (treatment arm 2) will provide suggestions comparable to that of a multi-professional care team (treatment arm 1).

3 Is this novel AI approach to e-CBT time and cost-efficient and comparable to the standard multi-professional healthcare decision-making team?

– We hypothesize that the AI approach will decrease the overall time and cost commitment of providing e-CBT.

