## Statistical analysis

4

Initially, all data will be examined for missing, nonsensical, and outlying variables. Missing data will not be attributed and will be treated as missing. All statistical analyses will be performed at the end of the trial and will consider a significance level of 0.05 and 95% confidence intervals. Analyses will be conducted to account for and assess differences across sex and gender identifications, and how these factors affect the adaptability and efficacy of e-CBT.

### Hypothesis 1: outcomes in depressive symptoms of treatment arm 1 will be comparable to treatment arms 2 and 3

4.1

Clinical outcomes of the healthcare teams’ decision (arm 1) versus the AI’s decision (arm 2), will be compared by assessing the treatment completion rate, number of completed sessions, and change in questionnaire scores. The completion rate across the two study arms and three levels of care will be calculated using a 2 × 3 × 2 contingency matrix (i.e., healthcare team vs. AI × 3 different treatment intensities × completers vs. dropouts) and chi-square analysis to compare within and between completion rates in the two arms. We will use a 2 × 3 (i.e., healthcare team vs. AI × 3 different levels of care) two-way analysis of variance (ANOVA) to compare the number of completed sessions across participant groups and care levels. Questionnaires are collected at 3 different times; at the start (for all participants), midway (for those who completed at least 6 sessions), and end of the study (for those who completed the treatment program). We will use a 2 × 3 × 3 (i.e., healthcare team vs. AI × 3 different levels of care × 3 time points) linear mixed-effects model for each questionnaire to compare clinical outcomes within and between groups and times. A mixed-effects model analysis will account for any missing data caused by participant dropout. Finally, we will assess if demographic covariables affect clinical outcomes using multiple 2 × 2 × 3 × 3 (demographic factors (e.g., male vs. female) × healthcare team vs. AI × 3 different levels of care × 3-time points for the questionnaire’s score) mixed-effects model to account for each demographic variable (i.e., sex, gender, age, and income). Bonferroni corrections will follow the ANOVA analyses in *post hoc* analyses.

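### Hypothesis 1 claims comparable depressive outcomes under AI and team allocation, but the plan fixes only difference tests at 0.05, with no margin and no rule for concluding comparability

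*Protocol article*

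**What the plan says.** The primary question is one of similarity. Research question 1 (section 2, Objectives) asks whether participants allocated by the AI will "show similar outcomes in depressive symptoms at 3 months to those allocated to an e-CBT program decided by a team of healthcare professionals". The hypothesis beneath it is "We hypothesize that the outcomes in depressive symptoms of treatment arm 1 will be comparable to the outcomes of treatment arms 2 and 3", and the heading of section 4.1 repeats it: "outcomes in depressive symptoms of treatment arm 1 will be comparable to treatment arms 2 and 3". The Introduction has the same aim for the algorithm: "This algorithm is expected to be comparable to the clinical decision-making process".

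The analyses fixed for this hypothesis in section 4.1 are:
- for completion, "chi-square analysis to compare within and between completion rates in the two arms";
- for the number of sessions, a two-way ANOVA;
- for the questionnaires, a "linear mixed-effects model for each questionnaire to compare clinical outcomes within and between groups and times", with Bonferroni-corrected post hoc comparisons.

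Section 4 sets the general rule: "All statistical analyses will be performed at the end of the trial and will consider a significance level of 0.05 and 95% confidence intervals". No margin, limit for the interval or criterion for comparability appears in the protocol.

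Section 3.10 derives the 186 participants from a paired t-test of PHQ-9 before and after e-CBT, applied to each of the six arm-by-intensity cells. Section 3.3 randomizes 93 to each of two arms; there is no arm 3.

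**The concern.** A test of no difference can reject equality, but it cannot establish similarity. Failing to reject is what one expects when the arms are alike, and also when they differ and the data are too sparse to show it. A claim of comparability needs a statement of how large a difference would still count as comparable, and an interval that excludes anything larger.

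Neither the test nor the sample size supplies this. The sizing shows whether patients improve within a cell, which they may do in both arms while one arm does clearly worse than the other. With 55% non-completion expected, the arm comparison could be imprecise. Imprecision makes a non-significant result more likely, so the error would favour the hypothesis. At stake is whether algorithmic triage can stand in for team triage.

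**Working it through.** **1. The plan's own figure.** Inputs from section 3.10: PHQ-9 16.2 before and 11.48 after, joint SD 5.45, power 0.8, completion 45%.
- Change = 16.2 − 11.48 = 4.72 points. Effect size = 4.72 / 5.45 = 0.866 (stated 0.86).
- Paired t-test, two-sided 0.05 (sidedness is assumed), effect 0.86: n = 13 gives power 0.812 and n = 14 gives 0.844. The stated 14 is adequate.
- 14 / 0.45 = 31.1 (stated 31), and 31 × 3 intensities × 2 arms = 186.

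The chain reproduces within rounding. None of its steps involves a difference between arms.

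**2. Precision of the arm comparison.** Assumption: 5.45 also serves as the SD for the between-arm comparison. SE = SD × √(2/n), and the 95% half-width is t × SE on 2n − 2 degrees of freedom. Two bounds for n:
- Completers only: 0.45 × 93 = 41.85, about 42 per arm. SE = 5.45 × √(2/42) = 1.19; half-width = 1.989 × 1.19 = 2.4 points, half of the whole 4.72-point change.
- All 93 per arm informative: SE = 5.45 × √(2/93) = 0.80; half-width = 1.973 × 0.80 = 1.6 points.

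**3. Chance of a non-significant result when AI allocation is truly worse** (two-sample t-test, two-sided 0.05, noncentral t):

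| SD | True deficit | 93 per arm | 42 per arm |
|---|---|---|---|
| 5.45 | 2 points | 30% | 62% |
| 5.45 | 2.36 points (half of 4.72) | 16% | 50% |
| 4.5 (assumed) | 2 points | 15% | 48% |
| 6.5 (assumed) | 2 points | 45% | 71% |

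**4. What a margin-based reading would deliver with 186 enrolled.** The documents give no margin, so these are illustrations. Non-inferiority, one-sided 0.025, true difference zero, SD 5.45:

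| Margin (points) | 42 per arm | 93 per arm |
|---|---|---|
| 2 | 38% | 70% |
| 2.36 | 50% | 84% |
| 3 | 70% | 96% |

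If two-sided equivalence is meant and both 95% limits must lie within ±2.36 points, the normal approximation, power = 2Φ(margin/SE − 1.96) − 1, gives about 2% with 42 per arm and 68% with 93.

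**The case against.** The strongest reply is that the protocol plans intervals as well as tests: it "will consider a significance level of 0.05 and 95% confidence intervals". A randomized between-arm estimate with a 95% interval does address research question 1. A reader might infer that the sponsor will treat p > 0.05 as proof that the AI is as good as the team, or that the trial cannot answer its first question at all. The documents support neither reading. They never say how a non-significant result will be interpreted, and the interval needed is already planned. What is missing is the limit to judge it against. Leaving that to an unseen analysis plan would not repair the mismatch, because the protocol itself fixes the hypothesis, the tests and the basis for the sample size.

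A second reply concerns size. The 42-per-arm case counts completers only. The mixed model also uses baseline and midway data, section 3.9 schedules the PHQ-9 at weeks 4, 7, 10 and 13, and adjusting for baseline could narrow the interval. This stands: 42 is the pessimistic end, and only a range can be given. The SD of 5.45 is described merely as joint, and the SD of change depends on a pre-post correlation that the protocol does not report.

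Third, it would be too much to say that five outcomes compete for the primary conclusion. Section 2 already makes sessions and completion secondary, Hypothesis 1 concerns depressive symptoms, and the sizing uses the PHQ-9 alone. What remains is PHQ-9 against QIDS, and the listing of completion and sessions under Hypothesis 1 in section 4.1. The mention of arms 2 and 3 looks like a slip, since sections 3.1 and 3.3 clearly define two arms, but it stands in the hypothesis itself and needs correcting.

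**Conclusion.** The point holds and must be fixed. A comparability hypothesis is paired with difference tests, no margin and a sample size built on within-cell change. A non-significant arm difference would not support it at any sample size. With SD 5.45 assumed between arms, the interval half-width is about 1.6 to 2.4 PHQ-9 points, and a true 2-point deficit would be missed about 30% to 62% of the time. For SDs of 4.5 to 6.5 the range is about 15% to 71%. These figures assume a simple two-sample comparison with between 42 and 93 informative participants per arm.

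A reader might also infer that 186 is too few. That does not follow without a margin: at 3 points with near-complete data the trial would be well powered, and at 2 points with completers only it would not.

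**What to change.** 1. Restate Hypothesis 1, in section 2 and in the heading of section 4.1, as Arm 2 (AI) versus Arm 1 (team), and delete arm 3.
2. Name one primary contrast: the arm difference in PHQ-9 change, from the mixed model already planned, at one stated time point. Research question 1 says 3 months, the primary objective refers to the end of the 13-session programme, and section 3.9 has a separate 3-month follow-up; these must be reconciled.
3. Say whether non-inferiority or equivalence is meant. Conclude comparability only if the two-sided 95% confidence interval for that contrast excludes a margin that the sponsor justifies and fixes before unblinding: the unfavourable limit for non-inferiority, both limits for equivalence.
4. Make QIDS and AQoL-8D supportive, and have section 4.1 treat completion and sessions as secondary, as section 2 already does.
5. State the power of 186 participants for the chosen margin.

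The cost is a wording change plus one power calculation, and no increase in enrolment is required. The price is candour: the trial may report an inconclusive result. At an illustrative non-inferiority margin of 2.36 points, power is about 50% to 84%, and it is lower if equivalence is meant.

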## Methods and analysis

3

### Participants

3.1

Participants (*n* = 186: *n* = 31 per e-CBT group * 2 arms) will be recruited at Queen’s University from outpatient psychiatry clinics at both Kingston Health Sciences Centre sites (Hotel Dieu Hospital and Kingston General Hospital), as well as Providence Care Hospital in Kingston, Ontario. Additionally, self-referrals and referrals from family doctors, physicians, and clinicians across Ontario will be accepted. After obtaining informed consent from the participant, the participant will be evaluated using the Mini International Psychiatric Assessment (MINI) through a secure video appointment to confirm a diagnosis of MDD using the Diagnostic and Statistical Manual of Mental Disorders, Fifth Edition (DSM-5) (41), by a trained professional on the research team.

All eligible participants will be randomized to receive a treatment plan based on the decision of either the healthcare team (Arm 1) or the Triage Module using an AI algorithm (Arm 2). Participants will be randomly allocated to one of the two arms of the study by a research assistant on the team who will also balance the group based on demographic variables (i.e., sex, gender, age, and income). Participants and therapists in the study will be blinded to which treatment arm the participant belongs to. By the nature of this study, participants and therapists will not be blinded to which treatment intensity the participant will receive since it will be evident whether the participant is receiving a phone/video call in addition to usual e-CBT care or pharmacotherapy. Each participant will be provided with an effective form of treatment (i.e., e-CBT) regardless of which group they will be allocated to. Participants will be informed that there is no incentive to join the program and that joining or withdrawing at any point will not affect them negatively. It will also be explained to the participants that the program is not a crisis resource and that they will not always have access to their therapists. In the case of an emergency, participants will be directed to proper resources, and this event will be reported to the study’s lead psychiatrist (principal investigator). All data will be anonymized and analyzed by research team members who are not directly involved in the patient’s care.

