### Inclusion and exclusion criteria

3.2

The inclusion criteria for this study are at least 18 years of age, diagnosed with MDD according to the Mini International Neuropsychiatric Interview 7.0.2 (MINI) that will be conducted by a trained research assistant. The MINI is a diagnostic interview that assesses 17 common mental disorders by following the diagnostic criteria of the Diagnostic and Statistical Manual of Mental Disorders, 5th edition (DSM-5) (41), ability to provide informed consent, ability to speak and read English, and having consistent and reliable access to the internet. The exclusion criteria include active psychosis, acute mania, severe alcohol, or substance use disorder, and active suicidal or homicidal ideation. Individuals with these disorders are less prone to having good insight into their thoughts; thus, e-CBT on their own may not be fit for them and would be better suited with therapist support throughout therapy. As for individuals with active suicidal or homicidal ideation, this program is not a crisis resource and individuals will be redirected to immediate support and resources that will better assist them. If a participant is receiving or has received CBT or e-CBT in the past year, they will also be excluded from the study to avoid confounding effects on the efficacy of this e-CBT program. If interested, participants excluded from the study will be linked to the appropriate resources.

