### Study design

3.3

If eligible for this randomized controlled trial, participants (*n* = 186) will be randomized (Figure 1) to receive an e-CBT treatment recommended by a multi-professional healthcare team consisting of a psychiatrist, psychiatric medical resident, and a trained research assistant (Arm 1, control group; *n* = 93), or the AI machine learning algorithm (Arm 2, experimental group; *n* = 93; Figure 1). To ensure blinding, all participants will complete the intake assessment by the healthcare team (Arm 1) and the Triage Module (Arm 2). Only the relevant data (i.e., Arm 1: intake assessment vs. Arm 2: Triage Module) will be analyzed depending on the treatment arm that the participant is randomly assigned to.

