#### Treatment arm 1: healthcare team allocation

3.3.1

Allocation of treatment intensity by the multi-professional healthcare team will be based on the following criteria:

The severity of symptoms/disability (DSM-5 criteria).Mental health factors (prior treatments and responses, current and past psychotic/manic episodes, current and past suicidal/homicidal ideation/attempts, family mental health history, past psychiatric history, and hospital admissions).Medical factors (current medical conditions and medications, personal and family medical history).Social factors (support system and living situation, and occupational, social, and personal functional impairment).

To assess the severity of MDD symptoms and the functional impairments, participants will complete the PHQ-9 and Sheehan Disability Scale (SDS) (42, 43) before the assessment appointment. The trained research assistant on the multidisciplinary team will conduct the assessment appointment and will relay the information to the rest of the team later to deliberate on treatment intensity allocation. All assessments will occur virtually through phone and video calls. Together, the healthcare team will decide whether the participant should be assigned to the e-CBT-only treatment, e-CBT treatment with weekly phone/video calls, or e-CBT treatment with pharmacotherapy. This process mimics the current triage process in clinical settings. To track cost-effectiveness, the trained research assistant will track the total duration of the individual assessment and team deliberation meetings for analysis of the total time commitment per patient.

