#### Treatment arm 2: AI algorithm allocation

3.3.2

Allocation of treatment intensity by the proposed AI algorithm will be based on the machine learning and natural language processing (NLP) of textual data provided by participants and their PHQ-9 score collected through a pre-treatment screening module called the Triage Module. This module, developed by the research team, (1) provides psychoeducation on the effects of psychotherapy, (2) collects PHQ-9 scores, and (3) asks participants six open-ended questions regarding their mental health history, their experiences with mental health disorders, and what mental health difficulties they are currently facing. Based on the participant’s answers to the open-ended questions, a variable called “Symptomatic Score” will be calculated using the NLP algorithm. If the PHQ-9 score < 19 and the Symptomatic Score > 0.75, the participant will be assigned to the e-CBT-only treatment group. However, if either the PHQ-9 score is >19 or the Symptomatic Score is <0.75, the participants will be assigned to the e-CBT treatment with weekly phone/video calls. If both scenarios occur and the PHQ-9 > 19 and Symptomatic Score < 0.75, then the participant will be assigned to the e-CBT treatment with pharmacotherapy. This NLP algorithm is patented by OPTT Inc. (International Patent System, PCT/US22/43514).

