To gather the relevant data (i.e., participant compliance and change in depression severity, as evaluated by the PHQ-9), the Triage Module was designed. As previously explained, NLP of the participants’ written accounts of their challenges with depression in the Triage Module will be used to calculate a Symptomatic Score. To verify the AI’s treatment allocation logic, completion rate and the change in PHQ-9 scores in a sample of participants (*n* = 190) who were previously enrolled in e-CBT-only treatment was assessed. The decision-making algorithm determined that the e-CBT-only program was suitable for 62 of the 190 participants (32.63%). Within these 62 participants, 53.22% (*n* = 33) had completed the e-CBT-only program in its entirety and only 20% (*n* = 12) had a final PHQ-9 score > 14. Furthermore, the algorithm indicated that e-CBT with telephone calls would be suitable for 100 out of the 190 participants (52.63%). Of the 100 participants, 41.0% (*n* = 41) completed the whole round of e-CBT-only therapy and 31.0% (*n* = 31) had a final PHQ-9 score > 14. Lastly, the algorithm indicated that e-CBT with video call was appropriate for 28 out of 190 participants (14.74%). Of these 28 participants, 35% (*n* = 10) completed the whole round of e-CBT-only therapy and 40% (*n* = 11) had a final PHQ-9 score > 14. The logic of the AI’s decision is therefore justified as those participants allocated to the e-CBT-only group had the highest percentage of completion and lowest percentage of final PHQ-9 scores >14 when completing e-CBT-only. Therefore, minimal therapist intensity is required for these individuals and e-CBT-only is sufficient. Conversely, participants allocated to the e-CBT with video call had the lowest completion rates and highest rates of final PHQ-9 scores >14 when enrolled in e-CBT-only. These findings justify the AI’s logic that greater therapist interaction is required. It is also important to note that demographic factors like age (below or above 40 years), biological sex (male or female) and income (less or more than CAD 50,000) did not have any significant effects on the number of sessions completed by participants (*p* = 0.92, 0.18, 0.90 for age, sex, and income respectively). The demographic factors did not affect the change in PHQ-9 score (i.e., the difference between the beginning and end of treatment scores) either (*p* = 0.20, 0.46, 0.39 for age, sex, and income respectively).

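### Allocation by a team research assistant is not separated from assessment and Arm 1 triage, and baseline PHQ-9 is not a balancing factor

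*Protocol article*

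**What the plan says.** On allocation, section 3.1 has participants randomly assigned to an arm "by a research assistant on the team who will also balance the group based on demographic variables (i.e., sex, gender, age, and income". Blinding to arm is promised there for participants and therapists; the allocator and the triage team are not mentioned.

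A research assistant appears in three other tasks:

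- Section 3.2, the MINI used to establish eligibility, "that will be conducted by a trained research assistant".
- Section 3.3, the Arm 1 decision team, "consisting of a psychiatrist, psychiatric medical resident, and a trained research assistant".
- Section 3.3.1, the intake interview: "The trained research assistant on the multidisciplinary team will conduct the assessment appointment". The same person reports the findings to the team and records how long assessment and deliberation take.

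Section 3.7 makes the care provider independent of the intake team. No similar statement covers the allocator.

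On severity, section 3.3.1 has the PHQ-9 completed ahead of the Arm 1 assessment. Section 3.3.2 uses it in the Arm 2 rule: "If the PHQ-9 score < 19 and the Symptomatic Score > 0.75, the participant will be assigned to the e-CBT-only treatment group". Section 2 makes change in PHQ-9 part of the primary objective. Section 3.3.2 also reports that, in 190 earlier e-CBT-only participants, age, sex and income "did not have any significant effects on the number of sessions completed by participants", and that they did not affect PHQ-9 change either.

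**The concern.** The article states an allocation procedure; it has not merely left one out. Someone on the team both assigns the arm and looks after balance on participant characteristics. Whoever does this without a system in between has to know the new participant's characteristics and the running balance by arm, and that knowledge can make the next assignment predictable.

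This trial is more exposed than most because the team's judgement is the Arm 1 intervention. If a team member knows or can guess the arm, four things can be influenced:

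- who is judged eligible;
- the care level chosen, and so the outcome comparison in section 4.1;
- the team-versus-AI agreement table in section 4.2;
- the recorded assessment and deliberation time that feeds the cost comparison in section 4.3.

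The hypothesis on outcomes is that the arms are comparable, and a bias at allocation can create similarity as easily as hide it.

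The second, smaller matter is the choice of factors. The arms are balanced on four demographic variables but not on the severity score that helps decide care level and from which change is measured.

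**Working it through.** **1. Roles side by side.** Allocator: a research assistant on the team (3.1). Eligibility interviewer: a research assistant (3.2). Intake interviewer and member of the three-role Arm 1 team: a research assistant (3.3, 3.3.1). The text does not say that these are one person, and it does not say that they are different people. Nor does it say whether the arm is assigned before or after the team settles on a care level. Figure 1, which might show the order, is not reproduced in the text reviewed.

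**2. How predictable balancing can be.** The balancing algorithm is not stated, so these are assumed scenarios: minimisation on four 50:50 binary factors, 186 participants, 300 simulated trials, and a guesser who holds the running tally.

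- Deterministic minimisation: about 85% of assignments are forced. Correct guesses: 0.85 + 0.15 × 0.5 ≈ 92%.
- Minimisation with a 0.8 biased coin: about 89% of assignments have a favoured arm. Correct guesses: 0.89 × 0.8 + 0.11 × 0.5 ≈ 77%.
- Simple randomisation: 50%.

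These figures show why the holder of the tally should stand apart from assessment and triage. They do not estimate what happened in this trial.

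**3. Chance imbalance in baseline PHQ-9.** Inputs from sections 3.3 and 3.10: 31 per cell × 3 intensities = 93 per arm, and 93 × 2 = 186, as stated. The change used for sample size is 16.2 − 11.48 = 4.72, and 4.72 / 5.45 = 0.866, against the stated 0.86. The 5.45 is described as a joint SD; using it as the baseline SD is my assumption.

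- SE of the arm difference = SD × √(2/n) = 5.45 × √(2/93) = 0.80.
- 95% range = ±1.96 × 0.80 = ±1.57 points. For an assumed SD of 4 to 6.5 it is ±1.15 to ±1.87.
- Relative to the 4.72-point change: 1.57 / 4.72 = 0.33.
- Probability that the arms differ by more than 1 point: about 21%.
- Completers only, 0.45 × 93 ≈ 42 per arm: 1.96 × 5.45 × √(2/42) = ±2.33. This treats completion as unrelated to severity and arm.

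**4. What balancing on PHQ-9 would gain.** In the same simulation, with baseline scores drawn as normal (mean 16.2, SD 5.45) and PHQ-9 split at 19 as a fifth factor, the 95% range falls from about ±1.5–1.6 to about ±1.0–1.1 points. N stays at 186.

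**5. How much of the imbalance reaches the result.** Section 4.1 plans a mixed model with the start score as one of three time points, so the comparison is of change. With equal variances at start and end, a baseline gap D shifts the change contrast by −(1 − ρ) × D, where ρ is the start-to-end correlation. The article gives no ρ, but for any positive ρ the shift is smaller than D. Over repeated randomisations it averages to zero.

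**The case against.** The strongest defence is that this is a condensed article. The sentence says allocation is random, and software stratification or minimisation operated by an assistant would fit it. Sequence generation and concealment are commonly left to the full protocol. The article also has real safeguards: everyone completes both the intake assessment and the Triage Module, expressly for blinding (3.3); care providers are independent of intake (3.7); the outcome questionnaires are completed by participants (3.9); and analysts are not directly involved in care (3.1).

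Much of this stands, and it rules out several stronger readings:

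- A reader might infer that balancing is done by hand and that concealment is broken. Neither is stated.
- A reader might infer that the allocator is the assessor. The article gives only the same job title.
- A reader might take PHQ-9 as the sole driver of care level. The Symptomatic Score shares that role in Arm 2, and Arm 1 also uses the SDS and mental-health, medical and social factors.
- A reader might call the demographic factors useless. Non-significant tests in 190 e-CBT-only participants do not show absence of effect, gender is not among the tests reported, and section 4.1 plans models by exactly these four variables, which is a reason to balance them.

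The defence does not remove the point about roles. The article names who allocates, places that person on the team, and protects the care provider's independence but not the allocator's. Doing both assessments on everyone blinds the participant; it does not by itself keep the triage team from knowing the arm.

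**Conclusion.** The point holds in two parts of unequal weight.

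The main part is that allocation, as written, is not separated from eligibility assessment, intake and Arm 1 triage, so neither concealment nor a triage decision made without knowledge of the arm is secured. Its size cannot be derived from the document. The predictability figures of 77% to 92% depend on assumed algorithms.

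The lesser part is that leaving out baseline PHQ-9 allows a chance difference of about ±1.6 points between arms of 93, if the baseline SD is 5.45. It would be wrong to read this as selection bias. It is random imbalance, and the planned mixed model absorbs much of it, so the cost is mainly precision.

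The change should be made. The text does not show that participants already enrolled were allocated improperly.

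**What to change.** For all remaining participants:

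1. Use a computer-generated, concealed allocation, by stratified blocks or minimisation with a random element.
2. Release it only after the team's care-level decision and the Triage Module output are both locked for that participant, through a system or an existing staff member outside recruitment, assessment and triage.
3. Add baseline PHQ-9 to the balancing factors. The demographic factors may stay.
4. Include the balancing factors in the primary mixed model.
5. Flag participants allocated under the previous method and run a sensitivity analysis on that split.

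The cost is an amendment, a short allocation program and no additional participants. Both assessments are already done on everyone. If the team currently deliberates only on Arm 1 participants, locking its decision for all adds staff time for the Arm 2 participants still to come; the paired agreement table in section 4.2 needs those decisions anyway. The main downside is two allocation methods within one trial, because recruitment began in December 2022.

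If the full protocol already specifies concealed software allocation by someone independent, correct the sentence in section 3.1 to say so. Balancing on baseline PHQ-9 can then be considered on its own merits.
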